## Abstract

**Background:**

Marital bereavement and separation or divorce are among the most stressful critical life events in later life. These events require a dissolution of social and emotional ties, adjustments in daily routine and changes in identity and perspectives for the future. After a normative grief or distress reaction, most individuals cope well with the loss. However, some develop a prolonged grief reaction. Internet-based self-help interventions have proved beneficial for a broad range of disorders, including complicated grief. Based on the task model and the dual-process model of coping with bereavement, we developed a guided internet-based self-help intervention for individuals who experienced marital bereavement, separation or divorce at least 6 months prior to enrolment. The intervention consists of 10 text-based self-help sessions and one supportive email a week. The primary purpose of this study is the evaluation of the feasibility and efficacy of the intervention compared with a waiting control group. The secondary purpose is to compare the effects in bereaved and separated participants. Furthermore, we aim to analyze other predictors, moderators and mediators of the outcome, such as age, psychological distress and intensity of use of the intervention.

**Methods:**

The design is a randomized controlled trial with a waiting control condition of 12 weeks and a 24-weeks follow-up. At least 72 widowed or separated participants will be recruited via our study website and internet forums. Primary outcomes are reductions in grief symptoms, depression and psychological distress. Secondary outcome measures are related to loneliness, satisfaction with life, embitterment and the sessions.

**Discussion:**

The trial will provide insights into the acceptance and efficacy of internet-based interventions among adults experiencing grief symptoms, psychological distress and adaptation problems in daily life after spousal bereavement, separation or divorce. Findings will add to existing knowledge by (1) evaluating an internet-based intervention specifically designed for spousal bereavement and its consequences; (2) testing whether this intervention is equally effective for individuals after separation or divorce; and (3) suggesting adaptations to improve the efficacy of the intervention, selective indication and adaptations for different needs.

**Trial registration:**

ClinicalTrials.gov, NCT02900534. Registered on 1 September 2016.

**Electronic supplementary material:**

The online version of this article (doi:10.1186/s13063-016-1759-5) contains supplementary material, which is available to authorized users.

## Background

Marital bereavement and separation or divorce are among the most stressful critical life events in later life. Both events imply a dissolution of social and emotional ties. This deeply affects the attachment system, and requires acceptance of the loss as well as the formation of a new identity and a new perspective for the future. Both events involve the adaptation of daily routines, which can be even more challenging when social, physical and financial resources decline in later life [1].

Grief and psychological distress after bereavement or divorce are normative reactions. For most people, grief intensity weakens to a manageable degree within several weeks or months. After the most intensive period, grief is still present but the loss becomes gradually integrated and no longer hinders the processes of ongoing life. However, some individuals are less able to cope with bereavement or divorce and show severe prolonged grief symptoms or adaptation problems lasting more than 6 months [2–5]. Some individuals even develop a persistent complex bereavement disorder, which is characterized by separation distress, frequent or disabling cognitive, emotional and behavioural symptoms, such as avoidance of reminders of the loved one, difficulties moving on with life and functional impairment [6, 7].

Several theoretical models describe factors that are crucial for an adaptive adjustment to bereavement. The task model identifies four tasks of mourning, namely, accepting the reality of the loss, experiencing the pain of grief, adjusting to an environment without the deceased person, and withdrawing emotional energy and reinvesting it in another relationship [8]. The dual-process model of coping with bereavement posits that a dynamic coping process oscillating between loss-oriented tasks, such as grief work, and restoration-oriented tasks, such as attending to life changes, is essential for adjustment [9]. Coping with loss-oriented tasks involves positive reappraisal versus rumination, revisions of personal goals, positive and negative event interpretation, and expressing emotions toward the deceased. Restoration-oriented coping is focused on attending to life changes, engaging in new activities, distracting from grief, and finding new roles and identities.

These models also provide a theoretical background for interventions ranging from self-help groups and pastoral care to psychotherapy. Cognitive-behavioural interventions for complicated grief are often based on three components: (1) exposure, e.g. the confrontational technique of ‘revisiting’ the deceased person or telling the story of the loss; (2) cognitive reappraisal or restructuring of individual dysfunctional thoughts (e.g., guilt, anger) associated with the loss; and (3) integration and restoration [10, 11]. Internet-based interventions increasingly complement grief counselling or therapy [12–15]. The majority of internet interventions combine the presentation of a web-based self-help programme with minimal but regular therapist contact. In a recent meta-analysis, this internet-based guided self-help approach has proved to be as effective as face-to-face therapy for depressive symptoms, social anxiety disorder and other psychological or somatic disorders [16]. Furthermore, internet-based interventions have advantages over face-to-face therapy. Benefits of internet-based approaches are low threshold accessibility, flexible usage, independent of time and place, usage at a self-determined pace, a high level of autonomy and privacy, and lower costs [17]. These factors may be especially relevant for older adults. However, challenges of internet-based interventions include technological problems and lower computer literacy or unease using computers, which may be more prevalent in old age.

Exposure, cognitive reappraisal, and integration and restoration as treatment components have also been implemented and evaluated in two randomized controlled trials of internet-based self-help interventions for complicated grief after bereavement. One 5 week internet-based intervention consisted of two writing assignments a week of approximately 45 min [12]. After every second assignment, participants received an email from a therapist with personal feedback and further instructions. This intervention addressed individuals who experienced symptoms of intrusion, avoidance, or maladaptive behaviour after the death of a significant other. The average age of the 55 participants was 37 years; all were women; 61% had lost a child and 10% their spouses. Effect sizes (Cohens *d*) for the comparison with the waiting group ranged from 0.96–1.74 for different outcome measures. Follow-up measures at 18 months confirmed the stability of these effects [18].

Another internet-based intervention comprised five structured confrontational writing assignments for individuals who experienced the death of a first-degree relative and who were significantly distressed [13]. The average age of the 757 participants was 43 years; 94% were women; 43% lost a child and 30% their spouses. Effect sizes ranged from 0.19 for emotional loneliness to 0.30 for positive mood for short-term follow-up and 0.25 and 0.23 for long-term follow-ups. These effects were mediated by lower rumination. However, grief and depressive symptoms did not improve. Risk and baseline distress were not confirmed as moderators.

In contrast with these two studies, Litz and colleagues evaluated an internet-based intervention focusing on self-care, social reengagement and goal-focused activities [14]. No formal exposure or cognitive reappraisal was included. Their randomized controlled trial targeted participants between 3 and 6 months after loss and aimed at exploring whether their intervention could prevent prolonged grief disorder. The intervention consisted of 18 sessions covering about 6 weeks, an initial phone call, and periodic brief emails from a therapist. The average age of the 84 participants was 55 years; 68% were women; 78% lost their spouses. The intervention resulted in Cohens *d* of 1.10 for the reduction in prolonged grief, 0.71 for depression and 0.51 for anxiety.

Finally, a recent study compared an internet-based exposure and behavioural activation treatment [15]. The therapist-guided interventions consisted of six homework assignments over 6–8 weeks and a short feedback after each assignment. The 47 participants were randomly allocated to the two active treatment conditions and a waiting control group. The mean age was 46 years; 92% were women; 40% reported the death of a partner and 60% reported other losses. Both interventions reduced complicated grief, post-traumatic stress, and grief rumination, but only exposure had an effect on depression and brooding levels relative to the control group. Effect sizes ranged between *d* = 0.07 and *d* = 1.2. The effects of both interventions were maintained at the 3-month follow-up assessment. To the best of our knowledge, no internet-based self-help intervention has been evaluated for divorced individuals.

### Objectives

Based on the task model of mourning, and the dual-process model of coping with bereavement, we developed a guided internet-based self-help intervention called LIVIA. This intervention addresses individuals who experienced marital bereavement or divorce at least 6 months prior to enrolling in the study and are seeking help for coping with prolonged grief symptoms, psychological distress or adaptation problems in daily life.

This study adds to existing knowledge by (1) evaluating an internet-based intervention specifically designed for spousal bereavement and its consequences; (2) testing whether this intervention is equally effective for individuals who suffer from grief and psychological or behavioural adaptation problems after a separation or divorce; and (3) by including loss-oriented tasks, i.e. exposure and cognitive reframing elements, as well as restoration-oriented tasks, i.e. self-care, social reengagement and goal-focused activities. The combination of both components may increase effect sizes compared with previous studies.

The severity of grief symptoms is not a criterion for taking part in the study, but will be analyzed as a moderator variable. We assume that the internet-based self-help intervention leads to beneficial effects across the severity dimension of distress. Individuals who have already developed a prolonged grief disorder, but who are not willing to see a counsellor or therapist, may benefit from the comprehensive internet-delivered intervention. For individuals with less severe distress, a timely intervention may help to prevent the progress from a normal grief or separation reaction to a prolonged grief disorder.

The objectives of the study are:To evaluate the effects of the guided internet-based self-help programme compared with a waiting control condition on:Grief symptoms, psychological distress and depression (primary outcomes)Loneliness, embitterment, satisfaction with life, and session-related outcomes (secondary outcomes)
To analyze moderators for the efficacy of the programme, i.e.:Spousal bereavement versus separation or divorceSeverity of grief symptoms, psychological distress and depression at baselineAge, sex and computer literacy
To explore mediators for the efficacy of the programme, i.e.:Frequency of use of the programme

## Methods

### Study design

This study is a randomized controlled trial with an internet-based self-help intervention and a waiting control condition. Figure 1 displays the study flowchart. The study population are adults who experienced marital bereavement or a separation or divorce more than 6 months prior to enrolment in the study. The self-help intervention is embedded in a larger Swiss population-based longitudinal study on relationships in later life, the LIVES study, IP 212 [19]. The study coordinator uses two separate lists for widowed and separated individuals, to allocate participants to one of the conditions based on computer generated random numbers using Random.org [20]. Participants in the waiting control group receive access to the intervention 12 weeks after the baseline interview. (The SPIRIT checklist is included as Additional file 1.)

**Fig. 1 Fig1:**
[figure not shown]
LIVIA flow chart study design

### Sample size

We specified the sample size needed for the different analyses conducting a power analysis based on a probability level of 0.05 and a power of 0.80 with G*Power [21] and a power analysis calculator for structural equation models [22]. To test the efficacy of the intervention compared with the control condition, we expected a large effect of *d* = 0.80. Power analyses indicated a necessary sample size of 42 individuals for this most basic analysis. For the analysis of several predictor variables, as well as moderation and mediation effects using structural equation modelling, we assumed moderate effects of *r* = 0.30. Power analyses resulted in a sample size of 138 participants. Anticipating a drop-out rate of 40% at the 6 month follow-up, we aim at recruiting between 72 and 220 participants at baseline.

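### The 42 behind the recruitment floor matches an undeclared one-sided test; an unadjusted two-sided 0.05 test at the plan's own d = 0.80 and 80% power needs 52 analysed

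*Protocol article*

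**What the plan says.** The Sample size section of the protocol article describes a calculation done with G*Power and "based on a probability level of 0.05 and a power of 0.80". For the comparison of intervention with waiting control the assumption is: "we expected a large effect of *d* = 0.80". The result is: "Power analyses indicated a necessary sample size of 42 individuals for this most basic analysis".

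The section then anticipates 40% drop-out at the 6-month follow-up and sets a recruitment range of 72 to 220 at baseline. The Methods part of the abstract repeats the lower end as a commitment: "At least 72 widowed or separated participants will be recruited".

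Three other places bear on the point:

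- Study design: waiting controls receive the programme 12 weeks after baseline.
- Measures: the first post-measurement (t1) is at 12 weeks, and the outcomes are also taken at baseline (t0).
- Statistical analysis: intention-to-treat multilevel regression with time, group, event and interaction terms, run in SPSS and Mplus.

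The article does not say whether tests are one- or two-sided, which test produced the 42, or what the allocation ratio is.

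**The concern.** A reader who puts d = 0.80, 0.05 and 80% power into a two-sample t test with the usual two-sided setting gets 52, not 42. The ten-person gap is what a switch from two tails to one produces. The coefficient tests of the planned regression are by convention reported two-sided. The size calculation and the analysis it is meant to support therefore do not appear to share the same test.

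The 42 appears to feed the lower recruitment bound, which the abstract states as the minimum for the trial. If recruitment ends near that bound, a null result on a primary outcome could be read as coming from a trial with 80% power when the usual two-sided reading gives less.

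**Working it through.** **Inputs.** From the Sample size section: d = 0.80, level 0.05, power 0.80, stated N = 42, 40% loss at 6 months, floor 72. Assumed here because the article does not give it: 1:1 allocation.

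**Formula.** For N analysed in two equal groups, the t statistic has N − 2 degrees of freedom and noncentrality d·√(N/4). Power is the probability that the noncentral t exceeds the critical value t(1 − 0.05/s; N − 2), where s = 1 or 2 is the number of sides. For s = 2 the negligible opposite tail is added.

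**Step 1: reproduce the 42 (one-sided).**
- N = 40: noncentrality 0.80·√10 = 2.530, critical value 1.686, power 79.9%. This is just short of 80%.
- N = 42: noncentrality 0.80·√10.5 = 2.592, critical value 1.684, power 81.7%.

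The smallest balanced total is 42, an exact match.

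**Step 2: the same inputs, two-sided.**
- N = 42: critical value 2.021, power 71.6%.
- N = 50: noncentrality 2.828, critical value 2.011, power 79.1%.
- N = 52: noncentrality 2.884, critical value 2.009, power 80.7%.

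The smallest balanced total is 52 (26 per arm). With 42 analysed, the effect detectable with 80% two-sided power is d = 0.89.

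**Step 3: other unadjusted two-sided tests.** A one-way ANOVA with f = 0.40 also gives 52, and a Mann-Whitney test about 54. None gives 42.

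**Step 4: link to the floor.** 42/(1 − 0.40) = 70, close to the stated 72. The two-sided counterpart is 52/(1 − 0.40) = 86.7, so 87, or 88 for equal arms.

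**Step 5: two-sided power from 72 recruited.** The 12-week loss is not stated, so a range is shown.

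| Loss by 12 weeks (assumed) | Analysed | Unadjusted two-sided power |
|---|---|---|
| 40% | 43 | 73% |
| 30% | 50 | 79% |
| 20% | 58 | 85% |
| 10% | 65 | 89% |
| 0% | 72 | 92% |

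The 52 are reached if loss is no more than 1 − 52/72 = 28%.

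**Step 6: effect of using the baseline score.** With pre-post correlation ρ, baseline adjustment raises the effective standardised effect to 0.80/√(1 − ρ²). At N = 42, two-sided:

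| ρ (assumed) | Effective d | Power |
|---|---|---|
| 0.4 | 0.873 | 79% |
| 0.5 | 0.924 | 83% |
| 0.6 | 1.000 | 89% (88.5%) |

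**The case against.** The strongest reply is that 42 is not a miscalculation. The article never says two-sided, its hypotheses are directional (reductions in symptoms, beneficial effects), and at one-sided 0.05 the figure is right. This stands as far as it goes: a reader might infer a plain arithmetic slip, and the article does not support that. It shows a figure whose basis is undeclared.

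A one-sided t test is also not the only route to about 42. A two-sided baseline-adjusted test needs 44 at a correlation of 0.4 and 40 at 0.5. A two-sided between-group test on three measures correlated 0.7 needs 42. The article states no such correlation and calls this the most basic analysis, so the one-sided t test is the likeliest explanation but not a demonstrated one.

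A reader might further infer that the trial's efficacy test simply has about 72% power. That does not follow, for three reasons. The figure belongs to an unadjusted two-sided t test on about 42 people, whereas the planned multilevel model draws on baseline scores and keeps participants with incomplete measurements. The 40% loss is tied to 6 months, while the randomised comparison ends at 12 weeks when controls gain access. And 72 is a floor in a range running to 220.

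Finally, a condensed article may leave the number of tails to a fuller document, and that omission alone would be no finding. What remains is a printed sample size that does not deliver the stated 80% under the usual two-sided reading unless an undeclared one-sided test or an undeclared correlation is supplied.

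**Conclusion.** The point holds in a conditional form. The 42 equals the one-sided two-sample t-test requirement, and no one-sided test is declared. Read two-sided and unadjusted, with 1:1 allocation assumed, the plan's own inputs require 52 analysed. That is ten more than stated, and 42 analysed gives 71.6% power against the stated 80%.

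Whether the floor of 72 falls short depends on loss by 12 weeks. Unadjusted two-sided power drops below 80% once that loss exceeds about 28%, and reaches about 73% if the whole 40% is lost by then. With little loss, with recruitment well above 72, or with an analysis that uses baseline scores at a moderate correlation, the target can be met. The article does not state the assumptions that would show this.

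**What to change.** Restate the sample-size paragraph in one of two ways.

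- **(a)** Give 52 analysed as the requirement for a two-sided 0.05 test at d = 0.80 and 80% power, which is 87 to 88 recruited if 40% are lost. Report the power that the floor of 72 provides for a stated loss at 12 weeks.
- **(b)** Base the power statement on a two-sided, baseline-adjusted comparison at 12 weeks, with the pre-post correlation stated and preferably shown over a range. The t0 scores are already collected.

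If a one-sided test was intended, say so and give the two-sided power next to it. Under any of these, name the test and the allocation ratio.

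The cost is wording. Option (a) may report a slightly less favourable power for the floor, and option (b) adds one assumption that has to be defended. Neither requires more participants or a change to data collection.

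### The upper recruitment target of 220 does not follow from the protocol's own figures (138 after 40% drop-out needs 230), and the floor of 72 covers only the basic efficacy test

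*Protocol article*

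**What the plan says.** The Sample size section of the protocol article works with "a probability level of 0.05 and a power of 0.80 with G*Power" and gives two separate requirements.

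- For intervention against waiting control: "we expected a large effect of *d* = 0.80", followed by "Power analyses indicated a necessary sample size of 42 individuals for this most basic analysis".
- For predictors, moderation and mediation by structural equation modelling: "we assumed moderate effects of *r* = 0.30", followed by "Power analyses resulted in a sample size of 138 participants".

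Both are then turned into one recruitment range: "Anticipating a drop-out rate of 40% at the 6 month follow-up, we aim at recruiting between 72 and 220 participants at baseline". The Methods paragraph of the abstract commits to the lower end only: "At least 72 widowed or separated participants will be recruited".

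The Objectives section lists the moderator analyses (type of loss, baseline severity, age, sex, computer literacy) and the mediator analysis (frequency of use). It does not make either depend on how many participants are recruited. The abstract's Background names the comparison of effects in bereaved and separated participants as the trial's secondary purpose.

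**The concern.** The range reads as two requirements, each inflated for the same drop-out: 72 for the 42, and 220 for the 138. If so, each end should return its requirement once 40% are lost. The upper end does not, so a stated sample-size figure conflicts with two others in the same paragraph.

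The second issue is which analyses the range supports. The trial can meet its recruitment commitment at 72 and still carry out every listed objective. A reader of the Sample size section would take the moderator and mediator analyses to have been planned at 80% power, yet nothing says that this power belongs only to the top of the range. At stake is how a null moderator result would be read, above all for the claim that the programme works equally well after bereavement and after separation. An underpowered comparison could be taken as evidence of no difference.

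**Working it through.** **Inputs, all from the Sample size section:** requirement A = 42; requirement B = 138; drop-out 0.40; range 72 to 220; level 0.05; power 0.80.

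**1. The plan's own figures.** The usual inflation is N recruited = N required / (1 − drop-out).

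| End of range | Required | Required / 0.60 | Stated | Stated × 0.60 |
|---|---|---|---|---|
| Lower | 42 | 70 | 72 | 43.2 |
| Upper | 138 | 230 | 220 | 132 |

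The lower end reproduces to within 2 participants and meets its requirement (43 against 42). The upper end is 10 short at recruitment and 6 short after drop-out.

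**2. Does another rule explain 220?**

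- Multiplying by 1.4: 138 × 1.4 = 193.2, which does not match.
- Multiplying by 1.6: 138 × 1.6 = 220.8, which is close, but the same rule gives 42 × 1.6 = 67.2 at the lower end, not 72.

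Neither rule yields both ends of the range.

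**3. Drop-out at which 220 would suffice.** 1 − 138/220 = 0.373, or 37.3%, against the stated 40%.

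**4. Size of the shortfall in power.** The figure of 138 cannot be rebuilt, because the article does not give the inputs to the structural equation calculator. I therefore assume that 138 gives exactly 80% power at a two-sided 0.05 level and that the noncentrality grows with the square root of the sample size:

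power(n) = Φ[(1.960 + 0.842) × √(n/138) − 1.960]

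- n = 132: 2.802 × 0.978 − 1.960 = 0.780, so power is about 78%.
- n = 43: 2.802 × 0.558 − 1.960 = −0.396, so power is about 35%.

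**5. Share of requirement B left at the floor.** 43/138 = 31%.

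**6. A limit on the lower-end check.** It takes the stated 42 as given. For a two-sample t-test with d = 0.80 and 80% power, 42 in total (21 per arm, power 0.817) corresponds to a one-sided test; a two-sided test needs 26 per arm, 52 in total. The article does not state sidedness. That is a separate matter and does not affect the upper-end arithmetic.

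**The case against.** **The floor was never meant for the 138.** This is right. The section sets out separate requirements for separate analyses, and 72 belongs to the 42. A reader might infer that the whole range misses its targets, but the documents do not support that: 72 leaves 43, which meets the 42. What stands is narrower. The article does not say that the other analyses depend on recruiting towards the upper end, although it lists them as objectives.

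**Counting only those who remain may be too strict.** The 40% refers to the 6-month follow-up, whereas the controlled comparison is at 12 weeks, before the waiting group gets access. The Statistical analysis section plans multilevel models, if data are missing at random, that use incomplete series. The effective loss may therefore be smaller. This softens the practical effect but does not rescue 220, because the Sample size section itself applies the 40% in setting the range.

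**The article condenses a fuller document.** That excuses omissions. It does not excuse a stated figure that conflicts with others in the same paragraph.

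**Two stronger readings should be set aside.** A reader might infer that so wide a range lets recruitment stop on favourable results and so inflates the type I error. The article mentions no look at outcomes during recruitment, and a closing rule is something it may leave to the full protocol. A reader might also judge power by a simple correlation of r = 0.30. By that yardstick about 85 participants suffice and 132 would have about 94% power, so it is not the calculation behind 138 and cannot be used to size the gap.

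**Conclusion.** The upper target is wrong as written: 230 must be recruited to keep 138 after 40% drop-out, and 220 keeps 132. The error is modest, about 2 percentage points of power (78% against 80%). The article does not show whether 220 is a slip or a deliberate ceiling.

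The lower bound is sound for the basic efficacy test on the protocol's own figure of 42. It does not support the predictor, moderation and mediation analyses, for which the committed minimum leaves about 43 of 138, or roughly 35% power. The counts 230, 132 and 43 follow directly from the stated figures. The two power values rest on the scaling assumption above and should be read as approximate. The efficacy test's own target is not affected.

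**What to change.** In the Sample size section:

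1. Change 220 to 230. Alternatively, keep 220 and state that it delivers 132 participants after 40% drop-out, with about 78% power if 138 gives exactly 80%.
2. State that 72 covers only the basic efficacy comparison.
3. State that, below 230 recruited, the moderator and mediator analyses are exploratory and carry no 80% power claim. If 220 is kept as the ceiling, this applies across the whole range.

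The abstract's minimum of 72 can stay once item 2 is in place. The cost is a few words and a slightly less favourable power statement. If 230 is adopted as the target, it also means up to 10 more participants at the top of the range.
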